## Methods/design

### Study design

This is a prospective, single-centre, open-label, randomised controlled study comparing active versus passive lifestyle intervention post kidney transplantation. All eligible kidney allograft recipients who meet the inclusion/exclusion criteria will be invited to participate. The duration of the clinical intervention in the study will be 6 months, with electronic data-linkage follow-up extending out to 5 years post study participation.

### Study setting

Patients will be recruited from a single transplant centre located in Birmingham, England, and it is planned to recruit 130 nondiabetic kidney allograft recipients. Birmingham, and the greater West Midlands region which it serves, contains a diverse multicultural population and this study is keen to ensure that study participation is representative of the population we serve. Therefore, we will strive to ensure adequate representation from the Black, Asian and Minority Ethnic (BAME) communities. Our dietitians have excellent experience of working with the local demographics in Birmingham and tailored information for the various BAME cohorts will be available via both the active and passive lifestyle intervention arms.

### Inclusion and exclusion criteria

#### Inclusion criteria

Aged 18 and overKidney allograft onlyFunctioning allograft (not on dialysis)Between 3 and 24 months post kidney transplantation

#### Exclusion criteria

Multiorgan transplant recipientPreexisting known diabetesPregnancyPhysically unable to undertake exercise assessments

### Study protocol and interventions

Potential participants will be identified through computerised search of medical records on patients attending clinic and from clinicians in charge of outpatient services. Relevant clinic lists will be reviewed on a weekly basis and potential participants identified (first approach will be from medical team or renal research nurse). Potential participants will be given the opportunity to reflect on the information given both verbally and within the written information sheet. No fixed time is specified for the length or timing of this prior interview as it will be dependent upon the patient’s understanding of their underlying disease, transplantation and complications, as well as their understanding of the research project.

Kidney allograft recipients who fulfil the eligibility criteria and give informed consent will be subsequently randomised into active versus passive intervention arms (at which point an OGTT is performed in each patient *after* randomisation and *before* intervention) (see Fig. 1). Randomisation will be facilitated through www.sealedenvelope.com, using random permuted blocks within strata to balance numbers and characteristics, into one of the following lifestyle intervention groups (*n* = 65 for each intervention group, total 130 participants):

**Fig. 1 Fig1:**
[figure not shown]
Trial design for the CAVIAR study showing randomisation arms comparing active versus passive lifestyle intervention in 130 nondiabetic kidney allograft recipients

*Active intervention group*. This group will receive active lifestyle modification intervention and will consist of dietitian referral, a graded exercise programme and weight-loss advice. Each patient will have four face-to-face appointments with the dietitian (lasting 45–60 min) at baseline, day 30, day 60 and day 120. Brief telephone reviews will be conducted between appointments (2–4 weeks after each face-to-face appointment) to review progress and provide additional support during the 6-month active intervention period (some appointments could be substituted with telephone support if wished by patient). Patients will have their diet reviewed by a dietitian and healthy eating advice will be given based upon guidelines issued by Diabetes UK [21]. The guidelines recommend a diet containing less fat and more fibre, based upon a meal framework of 50 % carbohydrate, 25 % protein (meat, fish, beans) and 25 % fibre (fruit and vegetables). Patients will be advised to keep food diaries to monitor compliance with initiated changes and will be followed up by the dietitians prospectively (using face-to-face appointments and telephone reviews) to monitor progress and reinforce the advice (in addition to routine clinic visits).In addition, a graded exercise programme will be encouraged to increase physical activity (e.g. endurance exercise such as walking, jogging, swimming) and an exercise diary will be encouraged to monitor compliance. To establish and prospectively monitor exercise habits we will perform Incremental Shuttle Walk Tests. Validated surveys to assess physical capability and activity (Duke Activity Status Index and GP Physical Activity Questionnaire, respectively) will be performed at each nurse-led assessment.The dietitian will be supported by our collaboration with a senior lecturer and consultant in addiction psychiatry, who has a recognised expertise in behaviour change therapy, and will support the behaviour therapy component of the active intervention arm. The behaviour change intervention will be developed in conjunction with the dietitians, and will utilise NLM tools developed from a Public Health England manual [22]. Based on the research evidence summarised above, it will include the following BCTs:Provide information on the consequences of suboptimal diet and exercise levels on health in generalProvide specific feedback of personalised information (body mass index, body fat percentage, waist/hip ratio) and comparison with the healthy rangePrompt intention formation, i.e. encouraging the patient to make a resolution to change their diet or level of exerciseSet specific goals around diet, exercise and weight (see Figs. 2, 3 and 4)Set graded tasks around the achievement of patient goalsEncourage self-monitoring of goals through food and exercise diaries and other Node-link mapsRegular review of specific behavioural goals, and reinforcement of progress through praise and encouragementReview of social support available from personal network of family and friends, and linking support to the achievement of specific goals.

**Fig. 2 Fig2:**
[figure not shown]
Intervention slide outlining patient dietary goals used to support the behaviour change element of the active lifestyle intervention

**Fig. 3 Fig3:**
[figure not shown]
Intervention slide outlining patient exercise goals used to support the behaviour change element of the active lifestyle intervention

**Fig. 4 Fig4:**
[figure not shown]
Intervention slide outlining patient weight goals used to support the behaviour change element of the active lifestyle intervention*Passive control group*. This group will be counselled about the risks of glucose intolerance and will receive leaflets outlining lifestyle modification advice. The leaflets include advice on healthy eating, exercise and the importance of weight loss. However, there will be no dietitian referral or focussed exercise and weight-loss monitoring review and no behaviour therapy intervention. Follow-up will be at routine clinic visits only where lifestyle modification advice will be reinforced as per usual clinical practice.

After 6 months of either intervention, both groups will undergo a repeat OGTT to assess any change in glycaemic status and metabolic physiological parameters. If any kidney allograft recipient develops PTDM during the course of the study, then they will be treated as per protocol (lifestyle modification advice with glucose-lowering therapy based upon individualised clinical assessment).

### Study outcomes

#### Primary endpoint

Difference in insulin secretion, sensitivity and disposition index

#### Secondary endpoints

Incidence of PTDMIncidence of impaired glucose toleranceIncidence of impaired fasting glucoseCommencement of glucose-lowering therapyDifference in glycated haemoglobin (HbA1c)Change in weight, body mass index, waist/hip ratio, triceps skin-fold thicknessChange in bioimpedance parameters (fluid, fat and muscle tissue mass and indexes)Change in blood pressure and lipid profileChange in physical activity (Incremental Shuttle Walk Tests, Duke Activity Status Index and GP Physical Activity Questionnaire, respectively)Change in psychological wellbeing (using two of three instrumental tools which have been validated in kidney transplant populations):EQ5D – quality of life and health status [23]Beck Depression Inventory (BDI-II) – specific tool for depression* [24]Situational Motivation Scale (SMS) – specific tool for assessment of situational motivation [25]Long-term clinical outcomes (patient survival, allograft survival, cardiac events, weight, etc) via electronic tagging to the electronic patient records at University Hospitals Birmingham (via Patient Registration number) and national registries (via NHS number)

*Patients will be offered leaflets with the clinical psychology department’s contact details if self-harm is reported.

#### Safety endpoints

Change in creatinineChange in proteinuria (urine albumin-creatinine ratio)

### Flowchart of investigations

#### Clinical data

Demographic data will be collected for each individual participant at the beginning of the study to record baseline clinical details. Pertinent clinical data (e.g. weight, waist/hip ratio, triceps skin-fold thickness, blood pressure, bioimpedance parameters (fluid, fat and muscle mass), etc.) will be collected at baseline and at follow-up at selected study points as demonstrated in Table 1.

**Table 1 Tab1:** Flowchart of study investigations

Investigations	Days post recruitment					Years post recruitment		
	0	60	90	120	180	1	3	5
	Randomisation		Mid-way point		Post intervention	Post intervention	Post intervention	Post intervention
Dietitian review with clinical psychology input (if active arm)	X	X		X				
Standard blood and urine tests^a^	X	X	X	X	X			
Baseline demographics^b^	X							
Clinical assessment^c^	X		X		X			
Patient-reported outcomes^d^	X		X		X			
Glucose	X	X	X	X	X			
Insulin	X		X		X			
Diabetes/obesity immunoassay^e^	X		X		X			
Triglycerides	X		X		X			
Oral glucose tolerance test	X				X			
HbA1c	X		X		X			
Electronic capture of clinical outcomes^f^						X	X	X

^a^Routine clinical blood and urine tests include renal function, tacrolimus levels, liver function tests, full blood count, urine albumin-creatinine ratio, etc.

^b^Extensive baseline data including cause of end-stage kidney disease, dialysis modality, dialysis duration, family history of diabetes, gestational diabetes, hepatitis C status, etc.

^c^Blood pressure, waist/hip ratio, weight, height, body mass index, bioimpedance (fluid, fat and muscle mass/index estimation), etc.

^d^Patient-reported outcomes (physical activity and psychological wellbeing as highlighted above)

^e^C-peptide, ghrelin, gastric inhibitory peptide (GIP), glucagon-like peptide-1 (GLP-1), glucagon, leptin, total plasminogen activator inhibitor-1 (PAI-1), resistin, visfatin and adiponectin

^f^Long-term clinical outcomes (patient survival, allograft survival, cardiac events, weight, etc) via electronic tagging to University Hospital Birmingham’s electronic patient records (via Patient Registration number) and national registries (via NHS number)

#### Biochemical data

Biochemical tests, to be done at baseline and follow-up (see Table 1) will include: plasma total cholesterol, low-density lipoprotein (LDL) and high-density lipoprotein (HDL) cholesterol, triglycerides, fasting glucose, urea and electrolytes, creatinine, full blood count, C-reactive protein (CRP), HbA1c, insulin and a range of diabetes/obesity biomarkers via a multiplex immunoassay (includes C-peptide, ghrelin, GIP, GLP-1, glucagon, leptin, total PAI-1, resistin, visfatin and adiponectin). The OGTT will obtain fasting blood samples for glucose in addition to routine clinic bloods after an overnight 12-h fast. Patients will then be administered 75 g of glucose (113 mL of Polycal®) with postprandial samples taken 2 h after glucose administration. The results of the test will be classified by current International Consensus recommendations for the diagnosis of PTDM [10], which mirror guidance in the general population for the diagnosis of diabetes [26].

#### Metabolic parameter assessments

Venous blood sampling from both baseline and follow-up OGTTs will be used to determine changes in insulin sensitivity, insulin secretion and the disposition index (interrelationship between both insulin sensitivity and secretion). The following formulae will be utilised for determination of these parameters of glucose metabolism:$$ \underline {Insulin\kern0.5em  secretion}=HOM{A}_{sec}= Insuli{n}_0\times \kern0.5em \left[ 3.33\kern0.1em /\kern0.1em \left( glucos{e}_0- 3.5\right)\right] $$$$ \begin{array}{ll}&{Insulin\kern0.5em  sensitivity}= McAuley's\kern0.5em  index= exp\\ &\qquad\qquad\qquad\qquad\qquad \times\left[\mathit{ 2. 6 3}-\left( \mathit{0. 2 8}\kern0.5em \times \kern0.5em  In\kern0.5em \left\{ {\mathit{insulin}}_{\mathit{0}}/ \mathit{6. 945}\right\}\right)\right.\\&\qquad\qquad\qquad\qquad\qquad-\left.\left(\mathit{ 0. 31}\kern0.5em \times \kern0.5em  In\kern0.5em  {\mathit{trigycerides}}_{\mathit{0}}\right)\right]\end{array} $$$$ \begin{array}{l}\underline {Disposition\kern0.5em  index}=HOM{A}_{sec}\times McAuley\mathit{\hbox{'}}s\kern0.5em  index= In suli{n}_0\times \left[ 3.33\kern0.2em /\kern0.1em \left( glucos{e}_0- 3.5\right)\right]\kern0.5em \times \kern0.5em \\ {} exp\kern0.5em \left[ 2.63-\left( 0.28\kern0.5em \times \kern0.5em  In\kern0.5em \left\{ insuli{n}_0/ 6.945\right\}\right)-\left( 0.31\kern0.5em \times \kern0.5em  In\kern0.5em  trigyceride{s}_0\right)\right]\end{array} $$

Surrogates for insulin sensitivity [27] and disposition index [28] have previously been validated and reported in the context of kidney transplantation. In addition to allowing us to determine the difference between active versus passive lifestyle intervention, comparison of baseline and follow-up glucose metabolic parameters will provide some insight into underlying pathophysiological mechanisms that lead to progression of abnormal glucose metabolism post transplantation.

#### Electronic data capture

Patients will be consented to electronic data capture of clinical parameters (e.g. weight, body mass index, creatinine, etc) from the electronic patient records of University Hospitals Birmingham at 1, 3 and 5 years post recruitment (utilising individual unique Patient Registration number). In addition, clinical outcomes (e.g. patient survival, allograft survival, hospitalisation, cardiac events, etc) will be electronically captured from Hospital Episodes Statistics for the same time points (utilising NHS number). This will allow long-term data capture without direct patient involvement and allow us to investigate the long-term effects of study interventions beyond the initial study intervention period.

#### Sample size

The principle parameters being examined in this study are changes in insulin sensitivity and insulin secretion. Our power calculation was performed with the assumption of a 20 % dropout rate and on the basis of an intention-to-treat analysis. We anticipate changes in the primary outcome measure from 5 % in the control group and 25 % in the intervention group. These figures are based on intrasubject variability of 25 % for insulin secretion and 20 % for insulin sensitivity, as previously utilised in a different randomised controlled trial in a post-transplantation setting [29].

Therefore, if we assume 80 % of the control group will demonstrate a 5 % change in the primary outcome measure (and 20 % dropouts demonstrate no change), then the average change in the control group is 4 %. Similarly, if we assume 80 % of the intervention group will demonstrate a 25 % change in the primary outcome measure (and 20 % dropouts demonstrate no change), then the average change in the intervention group is 20 %.

To detect this difference of 16 % change (assuming standard deviation of change is 25 %), we calculate that a total of 130 patients are required (65 per randomised arm) for 95 % power (assuming a 5 % significance level and a two-sided test) for a high-powered sample size.

#### Statistical analysis

Normality of data will be assessed using the Kolmogorov-Smirnov tests. The paired sample *t* test and the Wilcoxon signed rank test, for parametric and nonparametric data, respectively, will be used to compare the means of two variables from a single group. Comparison of data between groups will be made using unpaired Student’s *t* tests and the Mann-Whitney test for parametric and nonparametric data, respectively. Categorical data will be analysed using Pearson’s or Spearman’s test as appropriate.

We will use Cox proportional hazards regression to analyse survival outcomes. Additionally, for all primary and secondary analyses, we will carry out multivariable analyses using generalised linear models (adjusting for stratification factors). In this case, we will use the corresponding odds ratio to evaluate the adjusted size of the differences between proportions, by transforming back the estimated odds ratio associated with the treatment group into absolute differences in proportions. If the results of the analysis of the primary outcome are significantly affected, the adjusted effects will be taken as final. A *p* value <0.05 will be considered significant in the statistical analysis.

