### Specific research questions

This study is designed to answer four important questions relevant to kidney transplant recipients who are at risk of developing PTDM:Does lifestyle modification intervention improve glycaemic, cardiometabolic, clinical and physiological parameters in kidney allograft recipients?Is active dietitian-led intervention (incorporating a behaviour therapy approach) more effective than passive leaflet-driven guidance?Does active versus passive lifestyle modification improve patient-reported outcomes measures post kidney transplantation?Are there long-term clinical advantages beyond the 6-month intervention period for either active or passive groups?

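### A normality test picks the between-arm test, and the baseline value of each index is collected but not used as a covariate: precision is lost and the quantity estimated is not fixed

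*Protocol article*

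**What the plan says.** All of this is in the protocol article.

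- **Choice of test (Statistical analysis).** "Normality of data will be assessed using the Kolmogorov-Smirnov tests". Arms are then compared by unpaired Student's t "tests and the Mann-Whitney test for parametric and nonparametric data, respectively". Paired t or Wilcoxon signed rank tests are planned within a single group.
- **Adjusted models (Statistical analysis).** For all primary and secondary analyses there will also be "multivariable analyses using generalised linear models (adjusting for stratification factors"). The baseline value of the outcome is not named as a covariate, and no transformation is mentioned.
- **Which result counts (Statistical analysis).** "If the results of the analysis of the primary outcome are significantly affected, the adjusted effects will be taken as final".
- **Primary endpoint.** "Difference in insulin secretion, sensitivity and disposition index", with no scale stated.
- **Metabolic parameter assessments.** Changes in the three indices come from the baseline and follow-up OGTT samples. HOMAsec is fasting insulin × 3.33 / (fasting glucose − 3.5), and the disposition index is HOMAsec × McAuley's index.
- **Study protocol and interventions.** Patients are randomised, "at which point an OGTT is performed in each patient", before the intervention starts.
- **Sample size.** A 16-point difference in percent change, SD of change 25%, 95% power, two-sided 5%, 65 per arm.

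**The concern.** Two features of the stated analysis work against the primary endpoint.

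**The test is left to the data.** A t test concerns a difference in means; a Mann-Whitney test concerns a shift in ranks. Letting a normality test choose between them means that the quantity reported is unknown until the data are in. HOMAsec and the disposition index carry glucose − 3.5 in the denominator, so a right tail is built in and the gate will matter for them.

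**The baseline value is not used as a covariate.** It is measured in every patient, yet the simple tests cannot use it as a covariate and the models adjust for stratification factors only. Because the baseline OGTT comes after randomisation, the indices from it cannot be stratification factors. The rule for when the adjusted result becomes final does not cure this: it brings in no baseline value, and it is itself applied after the results are seen.

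At stake are the width of the confidence interval and the clarity of what the primary result estimates.

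**Working it through.** **1. The plan's own sample size.** With difference 16, SD 25, power 95% and two-sided 5%:

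n per arm = 2 × (1.960 + 1.645)² × (25/16)² = 2 × 12.995 × 2.441 = 63.4, so 64. The t-based version gives 64.4, so 65. Power at 65 per arm is 95.4% (t-based 95.2%). The stated 130 reproduces.

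**2. Gain from baseline adjustment.** With equal variance σ² at both visits and correlation ρ, a change score has variance 2σ²(1 − ρ) and ANCOVA has residual variance σ²(1 − ρ²). The ratio is (1 + ρ)/2. The article does not give ρ, so a range is assumed.

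| ρ (assumed) | Variance reduction | Effective SD | n per arm for 95% power | Power at 65 per arm |
|---|---|---|---|---|
| 0.3 | 35% | 20.2 | 42 | 99.5% |
| 0.5 | 25% | 21.7 | 48 | 98.8% |
| 0.7 | 15% | 23.1 | 54 | 97.7% |
| 0.9 | 5% | 24.4 | 61 | 96.3% |

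For example, at ρ = 0.5: 25 × √0.75 = 21.7.

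**3. Skewness of the indices.** If glucose falls from 4.5 to 4.2, the HOMAsec multiplier goes from 3.33/1.0 = 3.33 to 3.33/0.7 = 4.76, a rise of 43%. The same fall of 0.3 from 5.2 gives 1.7/1.4 = 1.21, a rise of 21%. The effect is steep at low glucose and milder nearer the middle of the range.

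Under assumed inputs (fasting glucose mean 5.0 to 5.3, SD 0.5 to 0.6; log-normal insulin with log SD 0.4 to 0.6; log-normal triglycerides; glucose of 3.6 or less excluded), skewness is about 6 to 8 for HOMAsec, 6 to 7 for the disposition index and 0.6 for McAuley's index. Log HOMAsec has skewness of about 0.2 to 0.5.

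**4. The planned rule against log-scale ANCOVA, for HOMAsec.** Assumed inputs: glucose mean 5.2, SD 0.40 between and 0.25 within patients; log insulin SD 0.45 between and 0.25 within; insulin 18% lower in the active arm; 65 per arm. The rule is Kolmogorov-Smirnov, then t or Mann-Whitney.

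| Analysis | Power |
|---|---|
| Log-scale ANCOVA | about 78% |
| Planned rule, percent change | about 71% |
| Planned rule, absolute change | about 61% |
| Planned rule, 6-month value | about 45% |

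Type I error of the planned rule stays near 5%. On percent change, the t and Mann-Whitney tests disagreed on significance in 11% of these trials. The inputs imply an SD of percent change near 49%, about twice the 25% in the Sample size section, so the power levels do not predict this trial's power; only the ordering and the rough gap are of use.

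**5. How often the gate rejects normality.** Across separate runs of these inputs, an uncorrected Kolmogorov-Smirnov test rejected in 26% to 46% of trials on percent change, 58% to 70% on absolute change and 76% to 93% on the 6-month value. With the Lilliefors correction it rejected in 90% or more on every scale. The article states neither the version nor the scale.

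**The case against.** The strongest reply is that the plan already uses baseline values: Metabolic parameter assessments speaks of changes, the sample size rests on percent change, and many secondary outcomes are listed as changes. That stands, and it makes percent change the fair comparator. The gap in the simulation is then about 7 points (78% against 71%), not the wider gaps on absolute change or the 6-month value. A change score still does not adjust for baseline.

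A second reply is that transformations and covariates belong in an unseen analysis plan. Where an article is silent, that would be right. Here it names the tests, the gate and the adjustment set, so the point concerns what is stated. The stratification factors are not listed, so adjustment for the baseline of some secondary outcomes cannot be excluded; for the OGTT indices it can.

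Four stronger readings are tempting, and the document does not support them:

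- **The trial is underpowered or its type I error is inflated.** Neither follows: the stated power reproduces and the error rate holds near 5%.
- **The choice of test is a coin flip.** The rejection rate runs from about a quarter to over 90% with scale and test version, so no single figure can be given.
- **All the primary indices are strongly skewed.** McAuley's index is not, under the same assumptions.
- **Paired tests are the only analysis of the first research question** ("Does lifestyle modification intervention improve glycaemic, cardiometabolic, clinical and physiological parameters in kidney allograft recipients"). The Statistical analysis section does not link them to that question, and the statement that "comparison of baseline and follow-up glucose metabolic parameters will provide some insight" concerns mechanisms of progression, not efficacy.

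**Conclusion.** The point holds as a loss of precision and an estimand not fixed in advance, and it should be corrected. The variance reduction of 35% to 5% rests on an assumed correlation of 0.3 to 0.9 and equal variances at the two visits. At the plan's own effect size and SD, it would raise power from 95.4% to between 96.3% and 99.5%, so the practical benefit is a narrower interval and reserve if the effect is smaller than assumed. The gain of about 7 points for HOMAsec rests wholly on assumed glucose and insulin distributions. That the baseline indices cannot be stratification factors, and that the gate decides between two different quantities, follows from the text alone.

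**What to change.** - For each primary index, pre-specify one ANCOVA of the 6-month value on the baseline value, treatment arm and stratification factors. Log-transform HOMAsec and the disposition index (outcome and baseline), and report a ratio of geometric means with 95% CI.
- Make this the primary result outright, in place of the rule that decides afterwards whether the adjusted effect is final.
- Drop the Kolmogorov-Smirnov gate and keep rank tests as sensitivity analyses only.
- Use baseline-adjusted ANCOVA for the other continuous outcomes.
- Label the within-arm paired tests descriptive.

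The cost is wording in the analysis plan. The baseline values are already collected, and neither the sample size nor the visit schedule changes.

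### Randomisation is stratified, but the default primary test ignores the strata, and an undefined criterion applied after both results are seen decides whether the stratum-adjusted result becomes final

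*Protocol article*

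**What the plan says.** Under Study protocol and interventions, the article allocates patients "using random permuted blocks within strata to balance numbers and characteristics". It does not name the stratification factors.

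Under Statistical analysis, three statements bear on the primary outcome:

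- "Comparison of data between groups will be made using unpaired" Student's t tests, or the Mann-Whitney test for nonparametric data. Neither has a stratum term.
- In addition, for all primary and secondary analyses, "we will carry out multivariable analyses using generalised linear models (adjusting for stratification factors").
- "If the results of the analysis of the primary outcome are significantly affected, the adjusted effects will be taken as final".

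The adjusted effect that the same paragraph goes on to describe is an odds ratio converted back to a difference in proportions. The primary endpoint (Study outcomes) consists of continuous measures: insulin secretion, insulin sensitivity and disposition index.

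**The concern.** Two analyses of the primary outcome are planned, and the one that counts is settled by comparing their results. The trigger could mean that the p value crosses 0.05, that the estimate moves by some amount, or that a formal comparison is significant. The article does not say which. Two analysts with the same data could report different final results and both claim to have followed the plan. The trial is open-label, so no blinding limits that judgement.

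The default is also the weaker of the two analyses. Blocking within strata balances the arms on the stratification factors and so removes their contribution to the chance difference between arms. A test that ignores the strata still counts that contribution in its standard error. If the strata are prognostic, its interval is too wide and its p value too large.

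Finally, the analysis that may become final is described only on an odds-ratio scale, which does not fit a continuous endpoint.

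**Working it through.** **1. The plan's own figure.** The Sample size section gives the difference and standard deviation ("To detect this difference of 16 % change (assuming standard deviation of change is 25" %), the error rates ("for 95 % power (assuming a 5 % significance level and a two-sided test"), and the result ("a total of 130 patients are required (65 per randomised arm").

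- Normal approximation: n per arm = 2 × (1.960 + 1.645)² × 25² / 16², which rounds up to 64, or 128 in total.
- Noncentral t: power is 0.949 at 64 per arm and 0.952 at 65 per arm.

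The stated 130 is reproduced. It is a calculation for an unadjusted two-sample comparison.

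**2. Standard error.** Let R² be the share of outcome variance explained by the strata. The documents do not give it, so a range is assumed.

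- Nominal standard error of the unadjusted test: 25 × √(2/65) = 4.39.
- True standard error under blocking within strata: 4.39 × √(1 − R²).
- The unadjusted standard error is therefore too large by the factor 1/√(1 − R²).
- Actual two-sided type I error of the unadjusted test: 2 × [1 − Φ(1.96/√(1 − R²))].

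**3. Power at the design effect.** The standardised effect is 16/25 = 0.64, so the difference over its nominal standard error is 0.64 × √(65/2) = 3.649.

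- Unadjusted: Φ[(3.649 − 1.96)/√(1 − R²)].
- Adjusted: Φ[3.649/√(1 − R²) − 1.96].

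| Assumed R² | True SE | Unadjusted SE too wide by | Type I error, unadjusted | Power, unadjusted | Power, adjusted |
|---|---|---|---|---|---|
| 0 | 4.39 | 0% | 5.0% | 95.4% | 95.4% |
| 0.1 | 4.16 | 5% | 3.9% | 96.2% | 97.0% |
| 0.3 | 3.67 | 20% | 1.9% | 97.8% | 99.2% |
| 0.5 | 3.10 | 41% | 0.6% | 99.1% | 99.9% |

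**4. Simulation.** Assumptions: 130 patients, four strata, blocks of four, normal outcome. The number of strata and the block size are not in the article. Results from several independent runs:

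- Type I error of the unadjusted test is 4.6 to 5.5% at R² = 0, 3.6 to 4.1% at 0.1, about 2% at 0.3 and 0.7 to 0.8% at 0.5. The adjusted model stays near 5% throughout (4.5 to 5.3%).
- Coverage of the unadjusted 95% interval under the null is 94.7% at R² = 0, 96.3% at 0.1 and 97.9% at 0.3.
- Claiming success whenever either analysis is significant gives a type I error of at most 5.7% in any run.
- At an effect of 0.64 the two analyses disagree on significance in at most about 1.6% of trials.

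**5. A smaller true effect.** At an assumed standardised effect of 0.45, which is not in the documents, the ratio is 0.45 × √(65/2) = 2.565. With R² = 0.3 the formulae give 76.5% power unadjusted and 86.6% adjusted. Simulation gives about 75% and 86%, with disagreement in about 11% of trials.

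**The case against.** The strongest reply has four parts.

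- **No false-positive harm.** Both analyses are named in advance and the adjustment set is limited to the stratification factors, so there is no free choice of covariates. A reader might infer that picking between them inflates type I error. It does not materially do so: even the most opportunistic choice gave at most 5.7%. This part stands.
- **The error is in the safe direction and may be nil.** A reader might infer that the default intervals are simply invalid. They are too wide, never too narrow, and only if the strata are prognostic. At R² = 0 nothing is lost, and nothing in the article supports an R² of 30 to 50%, especially for a percentage change from baseline. This stands, and it limits any claim about size.
- **Little power is lost as designed.** A reader might infer that the trial is underpowered by its default test. At the design effect the unadjusted test keeps about the promised 95% power or more at every R² examined. The gap reaches about 10 points only if the true effect is nearer 0.45. This also stands.
- **A journal article leaves detail to the analysis plan.** This does not stand. The article prints the selection rule itself, and that rule depends on the results. Further detail elsewhere cannot turn it into an advance choice unless the sentence is replaced or its trigger defined.

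It would also be wrong to say that the choice is left open until unblinding. The trial is open-label; the relevant moment is when the outcome results are seen.

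**Conclusion.** The point holds, as one that should be fixed rather than one that threatens the trial. Its core needs no assumed figure: the article allows two analyses of the primary outcome and chooses between them, after both are seen, by a criterion it does not define. The final estimate, interval and p value are therefore not determined in advance.

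The second part is conditional. The default analysis is conservative to the extent that the strata predict the outcome: type I error is about 5, 4, 2 or 1% at assumed R² of 0, 10, 30 or 50%. The cost at the design effect is about 0 to 2 points of power. These figures rest on assumed R², four strata, blocks of four and a normal outcome.

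**What to change.** In Statistical analysis:

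1. Delete the sentence that makes the adjusted result final on condition.
2. Name one primary analysis without condition: for each continuous primary measure, a linear model with treatment arm and the stratification factors, reporting the adjusted mean difference with its 95% interval and p value. Preferably include the baseline value of the measure as well; it is already collected at day 0. The calculations above do not test the gain from that addition.
3. Confine the odds-ratio and difference-in-proportions wording to binary outcomes.
4. Report the unadjusted t or Mann-Whitney comparison as supportive only.

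The cost is a short rewrite of one paragraph, made before the outcome data are analysed. No new data are needed. The sample size of 130 remains sufficient: at the design effect the adjusted model has about 95% power at R² = 0 and more above it.
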